## Abstract

**Background:**

Hemorrhoidal disease (HD) is associated with substantial economic burden and negative effects on health-related quality of life (HRQoL). The aCute HaemORrhoids treatment with MESoglycan (CHORMES) study aims to evaluate the effects of orally administered mesoglycan, a natural preparation of glycosaminoglycans with antithrombotic and profibrinolytic properties, as an acute treatment in patients with HD.

**Methods:**

CHORMES is a phase 2, double-blind, randomized controlled trial being conducted at two centers in Italy. Adults aged 18–75 years with Grade I–III HD according to Goligher classification or external thrombosed hemorrhoids, and a Hemorrhoidal Disease Symptom Score (HDSS) of ≥ 5, will be randomly allocated in a 1:1 ratio to mesoglycan or placebo and will be treated for 40 days (two capsules for the first 5 days and one capsule for the subsequent 35 days twice daily [after breakfast and dinner], equivalent to 200 mg in the first 5 days and 100 mg subsequently). Concomitant use of analgesics is permitted in both treatment groups. The trial aims to enroll 50 patients, with 25 patients in each treatment group. The primary objective of the trial is to evaluate the efficacy of mesoglycan in reducing symptoms of HD, assessed via change in HDSS from baseline (day 0) to day 40 in the intention-to-treat population. Secondary objectives include changes in HRQoL from baseline to day 40 using the Short Health Scale for Hemorrhoidal Disease, safety (adverse effects, physical assessments, vital signs and laboratory parameters in the safety population), fecal continence assessed using the Vaizey score, bleeding assessed using the Bleeding score, the amount and type of analgesic taken, and pain. Patient enrolment began on 11 December 2023, and trial completion is expected by December 2024.

**Discussion:**

The CHORMES trial will evaluate the efficacy and safety of mesoglycan, in addition to its impact on HRQoL, analgesic use and pain, in patients with HD. The results of the trial will assist clinicians in determining the most effective treatment for patients with HD.

**Trial registration:**

ClinicalTrials.gov NCT06101992. Prospectively registered on 26 October 2023 at https://clinicaltrials.gov/ct2/show/NCT06101992.

**Supplementary Information:**

The online version contains supplementary material available at 10.1186/s13063-024-08648-y.

## Administrative information

Note: the numbers in curly brackets in this protocol refer to SPIRIT checklist item numbers. The order of the items has been modified to group similar items (see http://www.equator-network.org/reporting-guidelines/spirit-2013-statement-defining-standard-protocol-items-for-clinical-trials/).

## Introduction

### Background and rationale {6a}

Hemorrhoidal disease (HD) is the most common proctological disease, with an estimated prevalence of 11–39%, peaking in individuals aged 45–65 years [1–3]. HD is associated with a substantial economic burden and can negatively affect health-related quality of life (HRQoL) [2, 4].

The most common presentation of HD is painless rectal bleeding occurring during or immediately after defecation [3, 5, 6]. Other symptoms, typically associated with prolapsed or large hemorrhoids, include rectal itching or swelling, a sensation of rectal fullness, fecal soiling, and pain [3, 5–7]. The Goligher classification system [8] is typically used to grade the severity of HD [3, 6]. This system is based on the presence and severity of prolapse, and ranges from Grade I (hemorrhoidal engorgement above the dentate line but no prolapse) to Grade IV (prolapsed hemorrhoids that cannot be reduced manually, possibly accompanied by inflammatory changes, mucosal atrophy, and ulceration). However, it is important to note that the Goligher classification system does not consider a wide range of symptoms, apart from bleeding in Grade I HD, special conditions such as pregnancy or inflammatory bowel disease, comorbidities or the presence of a single or circumferential prolapse, which may introduce bias and interobserver variability between physicians on assessing HD using the Goligher classification [9].

Effective treatments for Grade I–III internal hemorrhoids include diet and lifestyle modifications and medical treatments (e.g., topical glucocorticoids, vasoconstrictors, analgesics) and/or, in the event of failure, outpatient non-operative procedures such as rubber band ligation, sclerotherapy, and infrared coagulation [3, 5, 6, 10, 11]. In patients with thrombosed external hemorrhoids, topical vasodilators (e.g., nifedipine, glyceryl trinitrate) can relieve pain and reduce the size of the hemorrhoid [11]. If these treatments are ineffective, or in the event of high-grade and symptomatic hemorrhoids, surgical intervention is indicated [6, 10, 12]. Patients awaiting surgery can obtain relief through use of local or systemic anti-inflammatory agents [12].

Glycosaminoglycans (GAGs) are a heterogeneous family of polysaccharides that are essential components of the endothelium in blood vessel walls [13, 14]. As well as being key structural and functional components of connective tissues, GAGs have been shown to be involved in several biological functions, including embryonic development and regulation of cell signaling [13, 14]. Mesoglycan, which is extracted from the intestinal mucosa of pigs, is a natural preparation of GAGs that is rich in sulfur radicals with a strong negative electrical charge [14–16]. It consists of heparan sulfate (47.5%), dermatan sulfate (35.5%), chondroitin sulfate (8.5%), and slow-moving heparin (8.5%) [14–16], and is available in oral formulations or as a topically applied medical device (Prisma® Skin) [15, 17].

Mesoglycan exerts antithrombotic (activation of antithrombin III and heparin cofactor II) and profibrinolytic (stimulation of tissue plasminogen activator) activity by decreasing plasma fibrinogen concentrations without influencing prothrombin time, partial thromboplastin time, or other coagulation parameters [15, 16, 18–23]. Mesoglycan also promotes wound healing and has anti-inflammatory and anti-edematous effects [15, 16, 19, 22–25]. Mesoglycan has been shown to reduce thrombosis of mucocutaneous bridges after excisional hemorrhoidectomy in patients with Grade III–IV HD [16, 18], which may help avoid further surgery and reduce the risk of anal stenosis [26]. Additionally, the results of two preliminary Italian studies have suggested that mesoglycan effectively relieves symptoms (pain, itching, edema, inflammation, rectal bleeding) in patients with acute HD [27, 28].

While mesoglycan is widely considered to be useful for the treatment of acute HD (i.e., thrombosed external hemorrhoids) [11], the level of literature evidence in this patient population is not robust, and additional data are needed. As lifestyle changes (high water intake, diet rich in fiber, stool softeners) may provide meaningful improvements in symptoms in all phases of hemorrhoidal disease, a placebo-controlled trial design is appropriate. Therefore, the phase 2 aCute HaemORrhoids treatment with MESoglycan (CHORMES) trial is being conducted to assess the effects of mesoglycan as an acute treatment in patients with HD; herein, we describe the design of and rationale for the trial.

### Objectives {7}

The CHORMES trial aims to evaluate the efficacy and safety of mesoglycan versus placebo in patients with HD (Grade I–III or thrombosed external hemorrhoids). It will examine the effects of treatment on symptoms of HD and its impact on patient quality of life. Analgesic use during treatment and pain will also be assessed.

### Trial design {8}

In this phase 2 double-blind, randomized, controlled clinical trial, mesoglycan will be compared with placebo, with patients randomly allocated to either of these treatments in a 1:1 ratio. Patients will receive mesoglycan or placebo for 40 days, with assessment of effects at study site visits after 10, 20, and 40 days (± 2 days) of treatment. A follow-up assessment (for adverse events [AEs] only) at day 70 will also be performed via telephone.

## Methods: participants, interventions, and outcomes

### Study setting {9}

The trial is being conducted at two tertiary referral centers in Italy – Azienda Ospedaliero Universitaria Consorziale Policlinico, Bari, and Clinica Santa Rita di Vercelli, Presidio di Policlinico di Monza, Monza.

### Eligibility criteria {10}

#### Inclusion criteria

Adult patients (aged 18–75 years).Diagnosis of Grade I–III HD (according to the Goligher classification) or external thrombosed hemorrhoids.Hemorrhoidal Disease Symptom Score (HDSS) of ≥ 5.Female patients of childbearing age must agree to the use of an effective contraception method throughout the trial.

#### Exclusion criteria

Excluded patients are those with a medical history of:Coagulopathy (e.g., hemophilia A or B),Heart disease (e.g., atrial fibrillation, myocardial infarction),Chronic inflammatory bowel disease,Previous perianal surgery or other proctological pathology in the acute phase,Anal or colorectal neoplasms in the previous 5 years.

Excluded patients are those:Who are carriers of diathesis/hemorrhagic diseases,Who are pregnant,Who have received radiotherapy within the last 3 years or an anticoagulant or antiaggregant therapy,With galactose intolerance, Lapp lactase deficiency, or glucose-galactose malabsorption,Who have a contraindication to treatment or known intolerance to mesoglycan (or any of its excipients), or hypersensitivity to heparin and heparinoids.

### Who will take informed consent? {26a}

All patients must provide signed informed consent. Informed consent is being sought, obtained, and documented (in writing) by the Investigator in compliance with applicable regulatory requirements, Good Clinical Practice (GCP), and the ethical principles originating from the Declaration of Helsinki.

### Additional consent provisions for collection and use of participant data and biological specimens {26b}

Prior to starting the trial, the information sheet, informed consent form (Supplementary File S1), and protocol were submitted to the ethics committee of the Azienda Ospedaliero Universitaria Consorziale Policlinico, Bari (the coordinating center) and subsequently to the Clinica Santa Rita, Vercelli for review and approval (approval number 0067698). The trial was also approved by the Italian Medicines Agency (Agenzia Italiana del Farmaco, AIFA).

Investigators are ensuring that the privacy of patients, including their personal identity and all personal clinical information, will be maintained at all times. Personal clinical information will be treated as confidential in line with European Union privacy regulations, with patients identified only by individual identification codes in the electronic case report form (e-CRF) and other documents submitted to the Investigator. Data on the e-CRF, including personal clinical information, will be verified by the Monitor (an employee of the Contract Research Organization [CRO] Clinical Trial Consulting), persons specifically authorized by the Sponsor or by competent authorities.

## Interventions

### Explanation for the choice of comparators {6b}

Given the aforementioned anti-edematous, antithrombotic, and profibrinolytic actions of mesoglycan [15, 16, 18–25] and preliminary documentation of its clinical activity in patients with acute HD [16, 27, 28], it has been hypothesized that mesoglycan will effectively relieve symptoms of Grade I–III HD or external thrombosed hemorrhoids and improve HRQoL and will be associated with a low incidence and severity of AEs compared with placebo. Placebo has been chosen as the comparator in the trial because this will provide the clearest assessment of the benefits of mesoglycan in patients with HD [11, 12], while the concomitant use of analgesics and stool softeners in both treatment groups will be recorded to allow for the comparison between groups.

### Intervention description {11a}

Mesoglycan and placebo will be provided in boxes containing blister packs of 15 hard capsules each. The study drug will be identified by a unique batch number and expiry date. Each mesoglycan capsule contains mesoglycan sodium salt 50 mg (including heparin sulfate 47.5%, dermatan sulfate 35.5%, chondroitin sulfate 8.5%, and heparin slow 8.5%) plus excipients (lactose monohydrate, maize starch, croscarmellose sodium, magnesium stearate, gelatin, titanium dioxide, and erythrosine). The placebo capsules contain excipients (lactose monohydrate, maize starch, croscarmellose sodium, and magnesium stearate) and no active ingredients. Patients will take two capsules of mesoglycan or placebo for the first 5 days then one capsule for the next 35 days, twice daily (after breakfast and dinner). The total daily dose of mesoglycan will, therefore, be 200 mg in the first 5 days and 100 mg in the subsequent 35 days.

### Criteria for discontinuing or modifying allocated interventions {11b}

Treatment with the study drug may be discontinued spontaneously by the patient at any time or by decision of the Investigator, as the patient’s clinical condition suggests. For patients who discontinue the trial, a complete final evaluation will be performed, with results reported in the e-CRF alongside the reasons for discontinuation. Grounds for early termination of treatment included withdrawal of informed consent, protocol violations, and occurrence of serious/unexpected AEs or changes in health status that would interfere with the assessment of the trial or make it inappropriate to continue.

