### Sample size {14}

The trial aims to enroll a total of 50 patients (25 patients in each treatment group). This sample size is based on an assumed between-group difference in HDSS score of 1.8 points with a standard deviation (SD) of 1.7 (based on results of previous studies [31, 32]), an alpha of 0.05, and a two-tailed *t*-test with 90% power to reject the null hypothesis (i.e., the averages of the two treatment groups are equal) and an expected drop-out rate of approximately 10%.

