## Statistical methods

### Statistical methods for primary and secondary outcomes {20a}

The statistical analysis of data from the trial will be conducted by a statistician from CMV-Stat on behalf of the Sponsor.

All the variables will be analyzed descriptively using means with SDs, medians with interquartile ranges (IQRs), minimum and maximum values, and 95% confidence intervals (where appropriate) for continuous variables, and numbers, percentages, and missing data for categorial variables.

For all trial endpoints, analyses will be performed on each timepoint in absolute terms and as changes from baseline. Efficacy endpoints will be analyzed according to the stratification factor of the presence of uncomplicated HD versus thrombosed hemorrhoids. Efficacy analysis will be applied in the intention-to-treat (ITT) and per protocol (PP) populations and safety/tolerability will be assessed in the safety population. The ITT population is defined as all patients who have taken ≥ 1 dose of study drug/placebo and who have ≥ 1 post-baseline assessment for the primary endpoint. The PP population is defined as all enrolled patients who have data from all observations, met all inclusion/exclusion criteria, not taken any unauthorized drug, and taken ≥ 80% of the study drug/placebo. The safety population is defined as all patients who have signed informed consent and have taken ≥ 1 dose of study drug/placebo.

For the primary endpoint (i.e., change in HDSS from baseline to day 40 in the ITT population), the *t*-test will be applied with a significance level of 5%. If assumptions of normality and homoscedasticity are unmet, a corresponding non-parametric test will be applied.

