### Methods in analysis to handle protocol non-adherence and any statistical methods to handle missing data {20c}

Statistical methods for substitution of missing values will be listed in the SAP, which will be finalized in Version 1.0 of the SAP, before the database lock.

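### The protocol does not separate stopping study drug from leaving the trial, so about 5 of 50 patients may enter the primary day-40 analysis without a measured day-40 HDSS

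*Protocol article*

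**What the plan says.** All references are to the protocol article.

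- **Criteria for discontinuing or modifying allocated interventions {11b}.** It begins with the drug: "Treatment with the study drug may be discontinued spontaneously by the patient at any time or by decision of the Investigator". The next sentence concerns the trial: "For patients who discontinue the trial, a complete final evaluation will be performed". The section then returns to the drug: "Grounds for early termination of treatment included withdrawal of informed consent, protocol violations", followed by adverse events and changes in health status. It does not say when the final evaluation takes place, or what follow-up applies to a patient who stops only the capsules.
- **Trial design {8} and Table 1.** HDSS is scheduled at days 0, 10, 20 and 40. Day 70 is a telephone call for adverse events only.
- **Statistical methods for primary and secondary outcomes {20a}.** The primary endpoint is "change in HDSS from baseline to day 40 in the ITT population", tested by a t-test or a non-parametric counterpart. ITT membership requires one dose and at least one "post-baseline assessment for the primary endpoint".
- **Sample size {14}.** A difference of 1.8 points, SD 1.7, two-sided alpha 0.05, 90% power and "an expected drop-out rate of approximately 10" per cent lead to 25 patients per arm.
- **Missing data {20c}.** "Statistical methods for substitution of missing values will be listed in the SAP", which is to be "finalized in Version 1.0 of the SAP, before the database lock".

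**The concern.** A patient with a day-10 HDSS but none at day 40 belongs to the ITT set yet has no value for the primary test. A two-sample t-test on day-40 change cannot use that patient's day-10 or day-20 scores. The patient is either left out, which departs from the stated ITT set, or given a filled-in value.

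How to fill in a value is properly a matter for the SAP. Whether the day-40 HDSS is collected after drug is stopped is a matter for the protocol, because a SAP finalised shortly before database lock cannot recover assessments that were never made. The grounds for stopping include adverse events and changes in health status, which could differ between mesoglycan and placebo. If they do, the missing values are not a random loss and the treatment difference can shift. In a trial of 50, a handful of patients is enough to matter.

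**Working it through.** **1. The plan's own figure.** With difference 1.8, SD 1.7 (standardised effect 1.8/1.7 = 1.06), two-sided alpha 0.05 and 90% power, the t-test needs 19.76, so 20 per arm. Allowing for 10% drop-out, 20/0.90 = 22.2, so 23 per arm. The plan has 25, which is slightly conservative. The sample size is not in question.

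**2. How many patients are affected.** 0.10 × 50 = 5, or 2 to 3 per arm. About 90% of patients would have a measured day-40 HDSS.

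**3. Equal drop-out in both arms.**
- If those patients are left out, about 25 × 0.90 = 22.5 per arm remain and power is about 93%.
- If they are kept with filled-in values that carry only a fraction r of the treatment effect, the expected difference is 1.8 × [1 − 0.10 × (1 − r)]. With 25 per arm:

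| r (assumed) | Difference | Power |
|---|---|---|
| 0 | 1.62 | 91% |
| 0.5 | 1.71 | 94% |
| 0.75 | 1.755 | 95% |

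Power without any dilution is 95.6%. It falls below 90% only under harsher assumptions: at 20% drop-out with r = 0, the difference is 1.8 × 0.80 = 1.44 and power is 84%.

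**4. Unequal drop-out.** The documents give no drop-out by arm, no expected course of HDSS and no fill-in method, so every input here is assumed: a 4-point improvement by day 40 in both arms, 40% to 60% of it reached when the patient stops, and that value standing in for day 40.

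- Shortfall per patient: 4 × (1 − 0.6) = 1.6 to 4 × (1 − 0.4) = 2.4 points.
- False difference under no treatment effect = shortfall × difference in drop-out proportions.
- 16% versus 4% (4 versus 1 of 25, 10% overall): 1.6 × 0.12 = 0.19 to 2.4 × 0.12 = 0.29 points, or 11% to 16% of the planned 1.8.
- Extreme case, 20% versus 0% (all five in one arm): 1.6 × 0.20 = 0.32 to 2.4 × 0.20 = 0.48 points, or 18% to 27% of 1.8.
- Equal drop-out with the same shortfall: zero.

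The standard error with 25 per arm is 1.7 × √(2/25) = 0.48. Taking SD 1.7 as unchanged, shifts of 0.19, 0.29 and 0.48 raise the two-sided type I error from 5% to about 6.8%, 9.0% and 16.5%. The shift works against the arm with more drop-out, so it can favour either treatment.

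**The case against.** The strongest reply is that the text is silent rather than wrong. The final-evaluation sentence concerns patients who leave the trial. For them a last assessment is normal, and a later visit may be impossible, as after withdrawal of consent. Table 1 schedules the day-40 HDSS without excluding patients off drug. The per-protocol definition lists complete observations and at least 80% of drug taken as separate conditions, which fits patients who took too little drug but were still seen. The substitution method is left to a SAP that is not shown and could be multiple imputation. A t-test at a prespecified time point is a valid analysis for a small phase 2 trial.

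Much of this stands. A reader might infer that the final evaluation happens early, replaces the day-40 visit and has its score carried to day 40, so that the primary comparison rests on early or filled-in values and the ITT question cannot be answered. The documents do not support that. They give no timing, do not say that the evaluation replaces any visit, and name no carry-forward or single substitution. About 90% of day-40 values would be measured. Deferring the imputation method to the SAP is no fault.

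What remains is that no sentence commits the trial to a day-40 HDSS after drug is stopped, and that the ITT definition admits patients for whom the stated test has no outcome. Trial design {8} also counts its assessments in days of treatment, so the schedule does not settle the matter for patients off drug.

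**Conclusion.** The point holds as an ambiguity in follow-up combined with a primary test that cannot use a patient's earlier scores. About 5 of 50 patients may be in the primary set without a measured day-40 HDSS. If drop-out is near 10% and similar in both arms, the consequence is minor and power stays at about 90% or more. Bias needs drop-out, or its reasons, to differ by arm. Under the assumed 16% versus 4% split and a shortfall of 1.6 to 2.4 points, it is 0.19 to 0.29 points. Those inputs are illustrations, not figures from the plan. The change should be made because missed assessments cannot be recovered later and the remedy is cheap. The grounds for stopping treatment are not questioned.

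**What to change.** 1. In {11b}, separate stopping study drug from leaving the trial. State that patients who stop drug keep the scheduled HDSS assessments to day 40 unless they withdraw consent to follow-up. State that an earlier final evaluation is recorded at its actual time and not relabelled as day 40.
2. In {20a}, replace the primary t-test by a mixed model for repeated measures on HDSS at days 10, 20 and 40, with baseline HDSS, randomisation stratum, visit, treatment and treatment-by-visit. The day-40 contrast is primary. This uses scores the trial already collects, and keeps patients with a day-10 or day-20 score in the analysis without a filled-in value. Because it assumes that missingness is explained by the observed data, add a delta-adjusted or reference-based sensitivity analysis.

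Cost: recruitment has begun, so this is a protocol amendment that needs ethics approval before it is implemented, with matching SAP text, plus a few extra visits or calls for about 5 patients. No change to the sample size is needed.
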